
#### Control condition - treatment as usual (TAU)

Participants in the Control Condition will continue to complete treatment as usual (i.e. The Salvation Army residential substance abuse program).

#### Treatment fidelity

All intervention sessions will be audiotaped. Independent psychologists will rate a random allocation of 20% of treatment sessions for fidelity and competence.

### Outcome measures

A limitation with previous stepped wedge randomised controlled trials is that outcome assessment officers have not been blind to the treatment condition [33]. To ensure the blind measurement of the primary and secondary assessment measures, a combination of assessment officers will be involved in the study. Non-blind assessment officers will complete the face-to-face baseline assessments. This assessment will include administering the Structured Clinical Interview of the DSM 5-CT to identify 12-month and lifetime history of alcohol or other substance abuse and dependence disorders. The Timeline Follow-back and Opioid Treatment Index will be completed to examine use of alcohol and other substances before attending The Salvation Army program (OTI; [34]), ([35,36]). The baseline face-to-face assessment will also involve collecting demographic characteristics, physical health history and mental health history (see Table 1).

**Table 1 Tab1:** **Assessment instruments used for the current study**

**Domain assessment and instrument used**	**Week 1**	**Weeks 3 to 7**	**Week 8**	**Weeks 20, 32**
**Background and descriptive**				
Demographic information	✓			
Medical history (e.g. previous diagnosis of chronic diseases, family history of chronic diseases)	✓			
Mental health history (e.g. previous treatment, previous diagnosis, use of medication)	✓			
**Physical health**				
Body Mass Index (height and weight)	✓		✓	
Waist circumference	✓		✓	
Expired carbon monoxide	✓	✓	✓	
Blood pressure	✓		✓	
**Physical activity**				
International physical activity questionnaire	✓		✓	✓
Accelerometer	✓		✓	
Importance and confidence to increase physical activity	✓		✓	✓
**Diet**				
Healthy Eating Quiz	✓		✓	✓
Average servings of both fruit and vegetables over the previous 2-weeks	✓		✓	✓
Importance and confidence to improve diet	✓		✓	✓
**Alcohol and substance abuse measures**				
Structured Clinical Interview for DSM Disorders: Alcohol and Substance Use sections only	✓			
Addiction Severity Index: Alcohol and Drug composite scores	✓		✓	✓
Opiate Treatment Index	✓		✓	✓
Fagerstrom test for nicotine dependence	✓		✓	✓
7-day point prevalence of smoking	✓		✓	✓
Use of nicotine replacement therapy and number of quit attempts	✓		✓	✓
Smoking stages of change (Short Form)	✓		✓	✓
Importance and confidence to quit smoking	✓		✓	✓
**Mental health measures**				
Addiction Severity Index: Mental Health composite score	✓			
Quality of Life	✓		✓	✓

The non-blind assessment officers will also collect biomedical measures from participants who are attending the residential program at baseline and 8-weeks. This will include height, weight, blood pressure, waist circumference and expired carbon monoxide. Participants will also be asked to wear accelerometers (ActiGraph GT3X+) for a 5-day wear period from pre-midday Monday through to pre-midday Friday. This will ensure three full days of accelerometer wear (≥10 hours/day) data are collected – the minimum requirement deemed acceptable for analysis [37,38]. Each participant will be fitted with an accelerometer device, positioned over the non-dominant hip, affixed with an elastic band around the waist. Participants will be instructed to wear the device at all times except when bathing.

### Primary and secondary outcome measures

Independent assessment officers, blind to both the treatment condition and the design of the study, will conduct telephone interviews to complete the primary and secondary outcome assessment measures throughout the study. This will help to reduce bias associated with this type of study (e.g. participants are aware of their allocated treatment condition). Outcome measures will be collected at baseline, following the intervention (8-weeks) and then at 20 weeks and 32 weeks (3- and 6-months) follow-up. Each participant will be offered $20 AUD for completion of the baseline assessment and each subsequent follow-up assessment, as reimbursement for the time associated with completing the measures. For assessments completed while a participant is a resident at one of The Salvation Army programs, he or she will be remunerated in cash [39]. Due to the difficulties associated with posting cash payments, gift certificates will be posted to those participants who complete follow-up assessments once they leave the residential program.

The primary outcome measure will be the number of cigarettes smoked per day. Smoking reduction was selected as the primary dependent variable as this has been shown to be an important clinical strategy when working with long-term, heavy smokers towards smoking cessation. In a review of the smoking reduction literature, it was concluded that “smoking reduction increases the probability of later quitting” [40]. Smoking reduction is also likely to be associated with health and financial benefits for participants.

The secondary outcome measures will examine smoking, diet, physical activity and substance use. *Smoking -* 7-day smoking point prevalence abstinence self reported by participants. For participants who are still attending the residential program, abstinence will be verified by expired carbon monoxide tests (conducted by non-blind assessment officers). Participants will also be asked to report the number and duration of quit attempts since the last assessment time point, and readiness to quit smoking as measured by the Smoking Stages of Change (Short Form; [41]). Importance of and confidence in quitting smoking will be measured with two questions requiring ratings from 0 to 10: (1) How important is it to you personally to quit smoking?; (2) If you decided right now to quit smoking, how confident do you feel about succeeding with this? These scales have been adapted from motivational interviewing [42] and previously used to assess a variety of health behaviours (e.g. [43]). *Diet* – Participants will be asked to report the number of serves of fruit and vegetables that they usually eat each day, over the last 2-weeks. Fruit and vegetable consumption, as well as overall diet quality will also be assessed by the Australian Recommended Food Score (ARFS) index [44]. The ARFS uses a subsample of questions from the Australian Eating Survey Food Frequency Questionnaire [45] to assess adherence to eating patterns recommended in the Australian Dietary Guidelines for adults [46]. Importance of and confidence in improving diet were assessed with two questions requiring ratings from 0 to 10: (1) How important is it to you to improve your diet?, (2) If you decided right now to improve your diet, how confident do you feel about succeeding with this? *Physical activity* – The International Physical Activity Questionnaire (IPAQ) will be used to assess the participant’s self-reported amount of vigorous and moderate physical activity [47]. The IPAQ will also examine the amount of walking, as well as the amount of sedentary behaviour in the previous week. Importance of and confidence in increasing physical activity will also be assessed with two questions requiring ratings from 0 to 10: (1) How important is it to you to improve your physical activity?, (2) If you decided right now to improve your physical activity, how confident do you feel about succeeding with this?

### Data analysis

#### Power analysis

The primary outcome is number of cigarettes/day at 8 weeks follow-up. Unpublished pilot data suggests this has a SD of 12 cigarettes/day. Assuming a baseline/follow-up correlation of 0.25 we would need a sample of 85 before and 85 after intervention to give the study 80% power to detect a 5 cigarette/day intervention effect at a 5% significance level. We have added another 15% to allow for non-parametric distribution of the data, i.e. 98 people before and after. To account for loss to follow-up we have added another 40% (based on previous RCTs conducted by the researchers), providing a sample of about 140 people who will complete before and after measures.

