### Analysis plan

Since the number of clusters is small, we will use a fixed effects linear regression model to assess the effect of the intervention. The outcome variable will be number of cigarettes/day at 8 weeks, 20-weeks and 32-weeks. Baseline number of cigarettes/day will be included as a covariate. We will include a fixed effect for treatment centre, which accounts for differences in the average level of the outcome across centres and the association between before/after and centre induced by the stepped-wedge design. The main predictor of interest will be a before/after intervention variable, which would be at a different time point for each centre and will measure the intervention effect, which after adjusting for centre is a weighted average of the effect within each centre. Time will be included in the model as a continuous measure to account for any secular trends. We will use boot-strapped estimates of the standard error to account for any violations in the assumption of normality of residuals. The data will be analysed following the intent-to-treat principle. The primary analysis will be a complete case analysis, with sensitivity analysis undertaken to include all participants under an appropriate model for missing data such as multiple imputation. Analysis will be conducted independently by statisticians in the Clinical Research Design, IT and Statistical Support Unit, University of Newcastle.

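### The 80% power comes from a two-group formula; under the planned stepped-wedge model, with centre and calendar time adjusted for, power for 5 cigarettes/day is about one third

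*Protocol article*

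**What the plan says.** The Power analysis section ties the calculation to one time point: "The primary outcome is number of cigarettes/day at 8 weeks follow-up". Its inputs are a standard deviation ("Unpublished pilot data suggests this has a SD of 12 cigarettes/day"), a correlation ("Assuming a baseline/follow-up correlation of 0.25") and a test "at a 5% significance level". From these it asks for "85 before and 85 after intervention to give the study 80% power to detect a 5 cigarette/day intervention effect". Two additions follow. The first is labelled as being for the shape of the distribution: "We have added another 15% to allow for non-parametric distribution of the data, i.e. 98 people before and after". The second, 40%, is for loss to follow-up and brings the figure to about 140.

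The Analysis plan section then specifies a linear regression with baseline cigarettes/day, a before/after intervention indicator and two further terms: "We will include a fixed effect for treatment centre" and "Time will be included in the model as a continuous measure to account for any secular trends". The Study design section has every site begin as control and move to the intervention in a random, staggered order. The Study setting section gives four sites.

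**The concern.** The power paragraph and the analysis model describe different studies. A comparison of two independent groups uses the whole variance of the treatment indicator. In a stepped wedge, treatment is absent everywhere at the start and present everywhere at the end, and sites that cross early spend longer under intervention. Much of the variation in treatment is therefore explained by calendar time and centre. Once both are in the model, only the remainder informs the treatment effect. The Analysis plan itself acknowledges the association with centre that the design induces, but the sample size does not use it.

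If power is really far below 80%, a non-significant result says little about whether a 5 cigarette/day effect exists. A reader who relies on the stated power would take it as fair evidence that there is none.

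**Working it through.** **Inputs.** From the Power analysis: SD 12, correlation 0.25, difference 5, alpha 5% (taken as two-sided, which reproduces the stated figure), power 80%, 85 + 85 analysed. From the Analysis plan: baseline, fixed centre effect, linear time. From Study setting and Study design: four sites, all starting as control, crossing over in turn. Assumed, because the design figure is not available: one site per step, five periods, equal cells.

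**Step 1. Reproduce the stated figure.** For two independent groups with baseline adjustment,

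n per group = 2 × (1.96 + 0.84)² × 12² × (1 − 0.25²) / 5² = 84.8, rounded up to 85; power at 85 per group is 80.1%.

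Other readings do not fit: 91 without baseline adjustment, 136 for a change score, 68 for a paired comparison. So the 85 contains no allowance for the design. The next step is 85 × 1.15 = 97.75, which is the stated 98.

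**Step 2. Variance of treatment left after centre and time.** With 10 control and 10 intervention cells, the treatment indicator has variance 0.25.

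- Centre: the proportions of periods under intervention are 0.8, 0.6, 0.4 and 0.2. Their variance is (0.09 + 0.01 + 0.01 + 0.09)/4 = 0.05, so R² = 0.05/0.25 = 0.20.
- Time: the proportions of sites under intervention are 0, 0.25, 0.5, 0.75 and 1. Their variance is (0.25 + 0.0625 + 0 + 0.0625 + 0.25)/5 = 0.125, so R² = 0.50. These proportions are exactly linear in time, so categorical time gives the same result.
- The layout is balanced, so the two parts add: 0.25 − 0.05 − 0.125 = 0.075.
- Variance inflation = 0.25/0.075 = 1/(1 − 0.70) = 3.33.

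**Step 3. Power under the planned model.** The residual SD is 12 × √(1 − 0.0625) = 11.62. With N analysed and residual treatment variance v, SE = 11.62/√(N × v) and power = Φ(5/SE − 1.96).

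- N = 170, no adjustment for centre or time (v = 0.25): SE 1.78, power 80.1%.
- N = 170, centre only (v = 0.20): power 70.9%.
- N = 170, centre and time (v = 0.075): SE = 11.62/√12.75 = 3.25, power = Φ(1.54 − 1.96) = 33.6%. Simulation of the planned regression (5,000 runs) gives 34.3%.
- N = 196 (98 + 98), centre and time: power 37.8%.

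The difference detectable with 80% power at N = 170 is (1.96 + 0.84) × 3.25 = 9.1 cigarettes/day. The number needed for 80% power at 5 cigarettes/day is 169.5 × 3.33, about 565 analysed.

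**Step 4. Sensitivity to the assumptions.**

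| Assumption changed | Inflation | Power, N = 170 |
|---|---|---|
| Cells proportional to beds, all 24 site orders | 3.17 to 3.68 | 31% to 35% |
| Four periods, last site never crosses | 3.2 | 35% |
| Six periods, one extra intervention period | 3.36 | 33% |
| Seven periods, one extra control and one extra intervention period | 3.56 | 32% |
| Two sites per step, three periods | 4.5 | 26% |
| 5% to 20% of the variance lies between centres and is absorbed by the centre effect | 3.33 | 35% to 40% |
| Mean of the three follow-ups, assumed correlation 0.8 to 0.3 | 3.33 | 38% to 56% |

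**The case against.** The strongest objection is that the percentages rest on an assumed step layout. The text gives neither the number of periods nor the cell sizes. That stands as a qualification on the exact figure. It does not rescue the 80%, since every layout tried gives 26% to 35% at 170 analysed.

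The number analysed is also uncertain. The Power analysis chain from 98 to about 140 reads as per condition, while the Participants section expects about 140 for the whole study. If 140 is the total and 84 to 98 are analysed, power is about 19% to 21%. If 140 per condition were all analysed (280), it is about 50%. So one third belongs to 85 + 85 completers and must be labelled that way.

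The Analysis plan names outcomes at 8, 20 and 32 weeks. Pooling them helps, but it reaches only about 62% at 196 analysed under a favourable assumed correlation, and the power statement itself is fixed at 8 weeks.

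On clustering, the fixed centre effect removes between-centre variation, so an ordinary cluster design effect is not what this model needs. That is fair. What the model leaves uncovered is correlation within a centre and step, which would lower power further. The article gives no value for it, and none is used above.

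Finally, the article names no formula, so the two-group origin of the 85 is inferred from an exact numerical match. It also states no rule for reading a null result, so the risk of misreading is a judgement.

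**Conclusion.** The concern holds. The stated 80% belongs to a two-group comparison with baseline adjustment, not to the model in the Analysis plan. With four sites, one crossing per step, five equal periods and 85 + 85 analysed at 8 weeks, power for 5 cigarettes/day is about 34% (26% to 35% over the layouts tried), and 80% power applies to a difference of about 9.1. The time term causes most of the loss, but centre adjustment alone already brings power down to 71%. Neither the 15% nor the 40% addition was made for the design, and neither comes near an inflation of 3.33. This is a wrong figure in the article and should be corrected; it is not a detail that can be left to an analysis plan.

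**What to change.** Recompute power under the model in the Analysis plan (baseline, centre, calendar time) for the actual step layout and the expected number analysed in each site and period. Say whether 140 is the study total or the number per condition, because the result depends on it. Replace the 80% claim with that result. Under the layout assumed here and 85 completers per condition, it would read about one-third power for 5 cigarettes/day, or 80% power for about 9 cigarettes/day. State any assumed correlation within a centre and step. Add that a non-significant result will be interpreted from the confidence interval for the treatment effect.

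The cost is a rewritten power paragraph. No participants are added and the analysis model does not change, but the stated power becomes less favourable.

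### The 40% allowance for loss to follow-up is added to 98 instead of being divided out, so if 40% are lost, about 140 participants leave 84 completers and not 98

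*Protocol article*

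**What the plan says.** The Power analysis section defines the endpoint ("The primary outcome is number of cigarettes/day at 8 weeks follow-up"), its variability ("Unpublished pilot data suggests this has a SD of 12 cigarettes/day") and the adjustment for baseline ("Assuming a baseline/follow-up correlation of 0.25"). From these it concludes that "we would need a sample of 85 before and 85 after intervention" gives "80% power to detect a 5 cigarette/day intervention effect at a 5% significance level".

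Two allowances follow. The first: "We have added another 15% to allow for non-parametric distribution of the data, i.e. 98 people before and after". The second: "To account for loss to follow-up we have added another 40% (based on previous RCTs conducted by the researchers"). The section describes the outcome of this last step as "providing a sample of about 140 people who will complete before and after measures".

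Three other places bear on the point:

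- The Participants section gives approximately 140 as the number to be recruited over the whole study.
- The Analysis plan makes the primary analysis a complete case analysis and leaves multiple imputation to sensitivity analysis.
- The section on strengths and limitations describes this population as hard to follow up and lists measures to improve retention.

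**The concern.** An allowance for loss should be set so that the required number remains after the loss. If a fraction d is lost, the required number must be divided by 1 − d. Multiplying it by 1 + d gives too few, and the gap widens as d grows. At 40% it is large: a factor of 1.40 against 1.67.

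The error is not absorbed elsewhere. Because the primary analysis uses only participants with the outcome, the number of completers sets the power. A shortfall at this step removes the margin that the plan has just added for non-normal data.

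The sentence has a second difficulty. It describes the 140 as people who will have both measurements, whereas the Participants section gives about 140 as the number recruited. With any loss at all, 140 cannot be both.

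**Working it through.** **Inputs**, all from the Power analysis section: SD 12, correlation 0.25, difference 5 cigarettes/day, 5% significance, 80% power, a 15% allowance, then a 40% allowance. The section does not say whether the test is one- or two-sided; two-sided is assumed because it reproduces the plan's figure.

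**Step 1: reproduce 85.** With baseline as covariate, the residual variance is 12² × (1 − 0.25²) = 144 × 0.9375 = 135 (SD 11.62). For two groups:

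n per group = 2 × 135 × (1.960 + 0.842)² / 5² = 270 × 7.849 / 25 = 84.8, rounded up to 85.

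This matches. Other formulas do not: without baseline adjustment 91, change scores in two groups 136, a paired comparison 68, a one-sided test 67. So 85 is a number per condition.

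**Step 2: reproduce 98.** 85 × 1.15 = 97.75, rounded to 98. This matches.

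**Step 3: reproduce about 140.**

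| Operation | Result |
|---|---|
| 98 × 1.40 | 137.2, consistent with about 140 |
| 98 / 0.60 | 163.3, rounded up to 164; not consistent |

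The text says 40% was added, and the number agrees with that.

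**Step 4: what 140 delivers.**

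- At 40% loss: 140 × 0.60 = 84 completers. The shortfall is 98 − 84 = 14, or 14/98 = 14%. The result is also one below 85.
- Loss that 140 tolerates with 98 remaining: 1 − 98/140 = 30%.
- Loss covered by a factor of exactly 1.40: 1 − 1/1.40 = 28.6%.
- Check of the corrected figure: 164 × 0.60 = 98.4.

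**Step 5: power**, using power = Φ(5 / √(270/n) − 1.960), with n per condition. Where the 15% allowance is needed, n is divided by 1.15.

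| Basis | Completers per condition | Power, allowance not needed | Power, allowance needed |
|---|---|---|---|
| Planned | 98 | 85.4% | 80.2% (n = 85.2) |
| 140 per condition, 40% lost | 84 | 79.6% | 73.9% (n = 73.0) |
| 140 in total, equal split, 40% lost | 42 | 50.5% | 45.2% (n = 36.5) |

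For the last row, 98 per condition means 196 completers in total, and 196/0.60 = 326.7, or 327 recruits. These figures use the plan's own two-group formula and make no allowance for the centre and time terms in the model.

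**The case against.** The strongest objection is that the plan never says outright that 40% will be lost. It says that 40% was added. Read literally, 40% is the size of the increment, and 98/0.70 = 140 exactly, so the authors might have had 30% loss in mind. This cannot be excluded, and the 40% loss rate should be treated as an inference. But no 30% rate appears anywhere in the article, and a percentage tied to loss to follow-up and credited to earlier trials reads most naturally as a loss rate. If 30% was meant, the sentence misstates its allowance and still needs correcting. It is also true that 85/0.60 = 142 is close to 140, but the text applies the 40% after reaching 98, and that reading would discard the 15% allowance.

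A second objection concerns size. On the per-condition reading, 84 against 85 costs about half a percentage point if the 15% allowance proves unnecessary, and the planned analysis is linear regression with bootstrapped standard errors, not a rank test. This stands. The drop to about 74% is the lower end of a range on that reading and should not be quoted alone.

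A reader might also cite the 57% who leave the residential programs within three months as evidence that loss will exceed 40%. The article does not support this. The figure is early departure from treatment. The primary and secondary outcomes are collected by telephone, and reimbursement is posted to people who complete follow-up after leaving. It is not a follow-up loss rate and plays no part in this point.

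**Conclusion.** The inflation step is wrong as written. If 40% is the loss rate, about 140 participants give 84 completers where the plan calls for 98, and the figure on the same basis is 164. The arithmetic rests only on that reading of 40%; on any reading, 140 tolerates at most 30% loss.

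The effect on power depends on a basis that the article leaves unclear. If 98 and 140 are per condition, power is between about 74% and 79.6%, against the 80% stated. If 140 is the total, as the Participants section suggests, and the split is equal, about 42 completers per condition remain and power is about 50% even without the 15% allowance. A reader might infer that the trial definitely has 84 completers per condition, or definitely has half the power claimed. The article supports neither as a certainty, because it does not reconcile the two sections.

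The description of the 140 as completers contradicts the Participants section whichever basis is right. The point concerns the stated sample size and power; it does not affect the validity of the planned estimate.

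**What to change.** 1. Correct the inflation to n/(1 − loss): 98/0.60 = 164 on the same basis as the 98. Alternatively, keep 140, state that it yields 84 completers at 40% loss (or that it tolerates at most 30% loss), and restate the power to match.
2. State the expected loss rate as a rate, so that the allowance can be checked.
3. State whether 85, 98 and 140 are per condition or in total. The number of completers and the power in item 1 should be given only once this is settled: if 140 is the total, 84 is a total as well, and must not be reported as a per-condition figure.
4. Replace the wording that calls the 140 completers, so that it agrees with the Participants section.

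The cost is a few corrected sentences and a less favourable power figure. The article says that recruitment is already under way; restating power requires no extra enrolment, whereas holding to 98 completers at 40% loss would require a larger target.
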